## Abstract

**Supplementary Information:**

The online version contains supplementary material available at 10.1007/s00432-024-06057-x.

## Introduction

Whether laparoscopic surgery can be a clinically acceptable and alternative standard treatment for patients with colon cancer depends critically on long-term oncological outcomes (Ptok et al. 2014). The effects of laparoscopic versus open surgery on overall survival (OS) and other oncologic outcomes have been evaluated in a number of randomized controlled trials (RCTs) and meta-analyses of RCTs (Bagshaw et al. 2012; Bonjer et al. 2007; Nelson et al. 2004; Buunnen et al. 2009; Deijen et al. 2017; Fleshman et al. 2007; Jayne et al. 2010; Kitano et al. 2017; Lacy et al. 2008; Lacy et al. 2002; Theophilus et al. 2014; Di et al. 2013). Some of these RCTs evaluated only short-term (3-year) OS and revealed that laparoscopic surgery is non-inferior to open surgery (Study et al. 2004; Study et al. 2009; Lacy et al. 2002). Other RCTs evaluated long-term OS and mostly demonstrated an equivalent effect [Bagshaw et al. 2012; Deijen et al. 2017; Fleshman et al. 2007; Jayne et al. 2010; Kitano et al. 2017; Lacy et al. 2008]. However, some of these studies focused only on stage II and III patients, had an age restriction, were based on a small number of patients, had the problem of incomparability of results due to the use of an unusual study design, or did not separate colon cancer from rectal cancer (Fleshman et al. 2007; Jayne et al. 2010; Kitano et al. 2017).

The available evidence from previous RCTs and meta-analyses, however, revealed inconsistent and even contradictory stage-specific outcomes. One major limitation of the above-cited RCTs was that the estimated overall and stage-specific survival comparisons were based on only small numbers of at-risk patients. Lancy et al., for instance, showed the superiority of laparoscopic surgery over open surgery in terms of OS only in patients with stage III tumors (Lacy et al. 2008; Lacy et al. 2002). This even inspired the authors to propose a new hypothesis on how the less invasive surgery – as opposed to open surgery – could improve long-term oncological outcomes in patients with advanced, non-metastatic colon cancer (Lacy et al. 2008). However, Lancy and colleagues’ results were based on only 37 and 36 patients in the respective treatment groups (Lacy et al. 2008). This could be a possible reason why their finding was at odds with the results of a comprehensive meta-analysis of RCTs that showed a tendency toward better performance of open surgery in stage II patients (Theophilus et al. 2014). A post-hoc analysis of the European PETACC8 RCT contradicts this comprehensive meta-analysis as laparoscopic surgery was shown to be superior to open surgery in extending 5-year OS in patients with stage III colon cancer (Theophilus et al. 2014; Voron et al. 2021). The authors of the meta-analytic study were aware of their limited power to demonstrate the stage-specific effects of laparoscopic versus open surgery on 5-year OS, and they proposed using big real-world datasets to not only fill this gap but also to ensure the population-level applicability of the RCT results (Theophilus et al. 2014). Such a unifying approach to make decision-making more evidence-based and synergistic is in line with the recommendation of the GRADE working group (Schunemann et al. 2022; Schunemann et al. 2022).

On the other hand, a population-based retrospective cohort study conducted in the United States showed that for patients in stages I and II, laparoscopic colectomy outperformed open colectomy in terms of five-year OS, while there was no difference in stage III patients (Bilimoria et al. 2008). Benz et al. also reported, using nationwide registry data in Germany, that laparoscopic surgery resulted in a higher 5-year OS (Benz et al. 2017). Other observational studies have also shown that the laparoscopic approach provides at least as favorable results as the open approach after five years, even in elderly patients (Horie et al. 2021; Mazaki et al. 2021;  Volkel et al. 2018). It should be noted, however, that it remains likely that immortal time bias and biases arising from other sources can distort estimates presented by observational studies (Bykov et al. 2022; Suissa 2008). As such, the results of observational studies can even be misleading (Emilsson et al. 2018), and caution should be exercised when relying on evidence provided by such study designs. When comparing the two surgical treatment modalities, for example, differences in initial profiles of patients (patient selection) or the exclusion of a significant proportion of patients with incomplete data can lead to biased estimates (Bilimoria et al. 2008; Benz et al. 2017).

Common biases in observational studies such as immortal time bias, can be adequately addressed by emulating a hypothetical target trial (Emilsson et al. 2018; Hernan et al. 2016). Emulating a target trial can help answer comparative effectiveness and safety research questions in the presence of equivocal evidence from RCTs (Hernan and Robins 2016). In contrast to the ideal setting of RCTs, this rigorous study design allows to evaluate the impact of a particular intervention in a pragmatic (real-world) sense (Hernan and Robins 2016). Evidence shows that causal effect estimates derived from a carefully specified and emulated target trial are frequently similar to those obtained from RCTs (Kutcher et al. 2021). A successful emulation of a target trial using observational data can provide reliable evidence, which is particularly relevant when conducting an RCT is not feasible, ethical, or timely or when the generalizability of results from RCTs is unclear (Hernan and Robins 2016). Hernán and colleagues showed that targeted trials can reduce bias risks (immortal time and selection bias) and provide more accurate causal treatment effects (Hernan et al. 2016; Hernan and Robins 2016). This is done by choosing a time-zero that synchronizes follow-up start with eligibility assessment and treatment allocation, and then applying statistical methods to ensure comparability and randomness in treatment allocation (Hernan et al. 2016; Hernan and Robins 2016). Strict implementation of such a procedure at baseline corresponds to randomization in RCTs. Hence target trial emulation provides a novel option to evaluate the long-term comparative effectiveness of therapeutic interventions (Antoine et al. 2023).

In this study, we will use data from the Mecklenburg-Western Pomerania (MV) Cancer Registry to explicitly emulate a hypothetical target trial study that compares 5 year OS between laparoscopic and open surgical treatment strategies in patients diagnosed with stages I–III colon cancer. To this end, a target trial is specified that will randomly assign patients with solitary, non-metastatic colon cancer to either laparoscopic or open surgery, and then emulate this target trial using the cancer registry data over the period of 2008 to 2018. Treatment period- and stage- specific results will also be provided.

## Methods

### Research question

Does laparoscopic colectomy improve the 5-year overall survival rate compared to open colectomy in patients with stage I–III colon cancer?

### Study setting, data source, and study population

A major step toward raising and improving the standard of care in oncological health services in Germany was the nationwide implementation of clinical cancer registries, enacted by the Cancer Early Detection and Registry Act (Krebsfrüherkennungs- und -registergesetz, KFRG) in April 2013 (Federal Ministry of Health of Germany 2013). This emulated target trial study will use data from the Mecklenburg-Western Pomerania Cancer Registry, a registry providing ≥ 90% completeness of coverage (Arndt et al. 2020).

The estimated population of Mecklenburg-Western Pomerania was 1,629,464 inhabitants as of December 31, 2023 (Statistical Office of Mecklenburg-Western Pomerania 2024). The federal state covers 23,294 square kilometers and is the least densely populated state in Germany, with only 70 people per square kilometer (Statistical Office of Mecklenburg-Western Pomerania 2024). There are currently 38 hospitals in the whole region, just five of which function as certified colorectal cancer treatment centers, Federal Statistical Office of Germany 2024; OncoMap 2024). Compared to all German federal states, Mecklenburg-Western Pomerania had the sixth highest age-standardized incidence rate (ASIR) of colorectal cancer in men and the fourteenth highest in women in the period 2019–2020 (Robert Koch Institute 2024). Between 2008 and 2022, the ASIR of colon cancer in the region was 33.6 per 100,000 population for men and 21.1 per 100,000 population for women 35 (Interactive report of Mecklenburg-Western Pomerania Cancer Registry 2024). Our study population consists of all adult patients with a confirmed diagnosis of primary stages I–III colon cancer between January 1, 2008 and December 31, 2018, who underwent major elective laparoscopic or open surgery (OPS codes 5–455, 5–456, 5–457, and 5–458) during this period (ICD-10-GM 2023). Figure1 below shows the present locations of the Registry’s catchment areas, detailed by the postcode area.

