### Design of the target trial and the emulated trial

To answer our research question, this study will follow a two-step implementation process. First, we designed a hypothetical target trial protocol to compare the effect of the surgical treatment modalities on 5 year OS in patients with stages I–III colon cancer. Next, we will use real-world data from the Cancer Registry in Mecklenburg-Western Pomerania to explicitly and validly emulate the prespecified target trial. Table 1 summarizes the components of the specified hypothetical target trial protocol and the corresponding planned emulated trial using population-based cancer registry data. Hernán and Robins outlined seven key components that are essential for specifying target trial emulation studies (Hernan and Robins 2016). It is, however, possible to add other components such as the research question and the aim of the study, as Martinuka and colleagues implemented in their COVID-19 study (Martinuka et al. 2023).

**Table 1 Tab1:** Components of the hypothetical target trial and the emulated trial

Study component	Target trial	Emulated trial
Research Question	Does laparoscopic colectomy improve the 5 year overall survival rate compared to open colectomy in patients with stage I–III colon cancer?	Same as target trial
Aim	Compare the 5 year OS of patients with stage I–III colon cancer treated by laparoscopic colectomy or open colectomy.	Same as target trial
Design	Phase III, multicenter, open-label, two-parallel-arms RCT	–
Eligibility	Patients with solitary, primary stages I–III colon cancer aged ≥ 18 years at diagnosis, with performance score (Eastern Cooperative Oncology Group, ECOG ≤ 2 or Karnofsky score ≥ 50%), and Charlson comorbidity index (CCI ≤ 2).	Patients with solitary, primary stages I–III colon cancer aged ≥ 18 years at diagnosis, with performance score ECOG ≤ 2 or Karnofsky score ≥ 50%, and laparoscopic or open colectomy within 3 months (90 days) after diagnosis. CCI is not documented by Mecklenburg-Western Pomerania Cancer (MV) Registry center.

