Exclusions	Body mass index (BMI) > 35 Kg/m², advanced local disease (T4), adenocarcinomas of the transverse colon and rectum (including that of appendix, hepatic flexure, splenic flexure, overlapping sites and unspecified cancer of the colon), multiple primary colon tumors, prior history of cancer in the past 5 years. However, patients with non-melanoma skin cancer (NMSC) as well as in situ tumors (ICD-10 codes D00-D09) and benign tumors (ICD-10^a^ codes D10-D36) will not be excluded. The following patients will also be excluded: patients who underwent emergency colectomy, patients with gastrointestinal stromal tumor (GIST), neuroendocrine cancers, sarcoma cases, or patients with previous abdominal surgery. Additional excluded cases include robotic colectomies (OPS = 5–987).	Advanced local disease (T4), patients diagnosed with subtypes of colon cancer located on the appendix (C18.1), hepatic flexure (C18.3), transverse colon (C18.4), splenic flexure (C18.5), or overlapping sites of the colon (C18.8), and all unspecified sites (C18.9) – as well as cancer of the rectosigmoid junction (C19) will be excluded. Patients with prior history of cancer in the past 5 years (except NMSC, in situ tumors (ICD-10 codes D00-D09) and benign tumors (ICD-10 codes D10-D36)) will be excluded. In addition, patients with an additional GIST diagnosis, neuroendocrine cancers, sarcoma cases, patients with previous abdominal surgery for malignant indications as well as patients treated with emergency or robotic colectomy (OPS = 5–987) will also be excluded. Since data on BMI, previous surgery for non-malignant indications and CCI are not available in MV cancer registry, we will not use these covariates as exclusion criteria.
Treatment strategies	1. Laparoscopic colectomy 2. Open colectomy	Same as target trial
Grace-period for treatment implementation	–	The first three months after confirmed stages I–III colon cancer diagnosis.
Treatment assignment	Randomization, at baseline	The patient’s assignment to one of the two treatment strategies will be non-random. But randomness will be emulated by cloning patients in both arms.
Outcome	Death from all causes over a follow-up period of 60 months from baseline (start of follow-up)	Same as target trial (5 year OS)
Type of outcome	Time-to-event data	Same as target trial

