Follow-up	Follow up begins at diagnosis and the random allocation of patients to either treatment arms and then scheduled follow-up information according to German S3- guideline for colorectal cancer (German Guideline Program in Oncology 2019).	Patients will be followed from time-zero (date of diagnosis) until death from any cause, last date of information or administrative censor date (31.12.2023), whichever will come first.
Censoring	Loss to follow-up, administrative censor date (31.12.2023).	Same as target trial
Causal contrast	Intention-to-treat effect, per-protocol	Observational analogue of the per-protocol effect
Effect measure	Hazard ratio (HR), mean survival time difference	Same as target trial
Analysis plan	Multivariable Cox regression, absolute risk difference and restricted mean survival time (RMST)	Inverse-probability weighted Royston- Parmar parametric survival model. Further to the HR, absolute risk-difference, RMST difference will be calculated.
Covariate adjustments	ϖ Socio-economic characteristics: Age at colon cancer diagnosis (in years) and sex. ϖ Clinical characteristics: UICC^b^ stage (I, II or III), treating institutions, tumor laterality (left or right), treatment period (2008–2009, 2010–2014, 2015–2018), performance score (ECOG = 0, 1, or 2), hospital classification (certified colon center or not), local residual tumor margin status (yes, no, or not assessable), grade (low, intermediate or high), and number of harvested lymph nodes (< 21 or ≥ 21).	ϖ Socio-economic characteristics: same as target trial. ϖ Clinical characteristics: same as target trial.
Sensitivity analysis	Excluding cases with missing values (complete case analysis, CCA)	Sensitivity analyses: - 1) Repeat the same analysis on patients with complete case data - 2) Including all advanced local disease (stage T4N0-2M0) cases - 3) Quantitative bias analysis using the E-value method to evaluate the effect of potential residual confounders (BMI, comorbidity, previous abdominal surgery for non-malignant indications)
Comparator analysis		Comparator analyses: - Comparator 1) DAGs-guided naïve analysis of using fully adjusted cox proportional hazards model - Comparator 2) An Inverse-probability-weighted regression-adjustment (Doubly robust) analysis

^a^ ICD-10 = The International Classification of Diseases, 10th Revision

^b^ UICC = Union for International Cancer Control

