Patients will be followed up from the date of assignment to either treatment modality until death from any cause (the outcome of interest), the last date of follow-up, or the administrative censor date (31.12.2023), whichever occurs first. This administrative censor date is chosen to ensure that patients are observed for at least five years. Patient follow-up will be made in accordance with the recommendation of the German S3- guideline for colorectal cancer (German 2019). In the emulated study, we will start following the patients at time-zero, which is defined as the time point at which the eligibility criteria will be met. The initiation of treatment will have to occur within the first three months after the diagnosis of colon cancer (defined grace-period). Follow-up will end on the date of death, last date of follow-up, or 60 months after time-zero, or the administrative censor date Dec. 31, 2023, whichever will occur first. The main outcome will be 5-year OS, which refers to the duration from time-zero until death from any cause. The estimated hazard ratio will be complemented by the mean survival difference (at 1, 3, and 5 years) between the patients treated with laparoscopic and open surgery, respectively. Since our study covers a long period of time (2008 to 2018), treatment period-specific analyses will be performed to mitigate potential bias that may be induced by changes in clinical knowledge and practice over time (Hou et al. 2022).

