In the web-based DAGitty environment (https://www.dagitty.net/), we will utilize directed acyclic graphs (DAGs) to determine the minimum necessary adjustment sets of confounders to control for within the comparative multivariable model. This approach mitigates the risk of bias that may arise from conditioning on intermediate covariates or colliders and mediators (Textor et al. 2011; Tonnies et al. 2022). The causal diagram for the comparative multivariable Cox model is complemented by a literature review and discussion to identify confounders, colliders, mediators and prognostic factors (Austin and Stuart 2015; Lederer et al. 2019). By adjusting the minimum sufficient adjustment sets of confounders in our comparative model, we will be able to block any backdoor bias paths (remove relevant confounding) when estimating the total causal effect of surgical treatment modality on all-cause mortality.

We will consider the following baseline characteristics (measured before or at time-zero) as potential confounders: Age at colon cancer diagnosis, sex, year of surgical treatment (classified according to the implementation and update series of the German S3- guideline for colorectal cancer (German Guideline Program in Oncology 2019) as 2008–2009 [pre-implementation], 2010–2014 [first update], or 2015–2018 [second update]), tumor laterality (right-sided [caecum and ascending colon] tumor or left-sided [descending and sigmoid colon] tumor), hospital type (classified as either a registered colorectal cancer center or other group), performance status (ECOG ≤ 2 or Karnofsky performance status score ≥ 50%), and histologic grade (low, intermediate or high), UICC stage (I, II or III), and local tumor size (T-stage). In addition, we will adjust the following two variables that serve as quality indicators of performed surgical procedure: minimum number of harvested lymph nodes (classified as < 21 or ≥ 21) (Choi et al. 2010), and local residual tumor status within 3 months of diagnosis (no (R0), yes (R1 + R2), not assessable or missing). We will also extract the following dates accurate to the month (date of birth, diagnosis, surgery, death, neo/adjuvant therapy initiation, and conversion to open surgery) and other covariates (project specific pseudonym, tumor IDs, cause of death).

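### Capping surgery as well as diagnosis at 31 December 2018 conflicts with the 90-day grace period, and year of surgery is listed as a baseline covariate although it is fixed after time-zero; the effect is small

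*Protocol article*

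**What the plan says.** All references are to the protocol article.

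- **Population** (Study setting, data source, and study population): a confirmed diagnosis of "colon cancer between January 1, 2008 and December 31, 2018, who underwent major elective laparoscopic or open surgery", with the procedure codes and their time limit given as "OPS codes 5–455, 5–456, 5–457, and 5–458) during this period".
- **Eligibility in the emulated trial** (Table 1): "laparoscopic or open colectomy within 3 months (90 days) after diagnosis". No calendar limit on surgery is given.
- **Grace period** (Table 1): "The first three months after confirmed stages I–III colon cancer diagnosis".
- **Time-zero** (Table 1): "Patients will be followed from time-zero (date of diagnosis) until death from any cause". The text after Table 1 words it differently: "time-zero, which is defined as the time point at which the eligibility criteria will be met".
- **Covariates** (Statistical analysis): the list opens with "We will consider the following baseline characteristics (measured before or at time-zero) as potential confounders" and includes "year of surgical treatment (classified according to the implementation and update series". The categories are 2008–2009, 2010–2014 and 2015–2018. Table 1 gives the same three under treatment period, and treatment-period-specific analyses are planned.
- **Cohort in the Discussion**: defined by diagnosis between 2008 and 2018, with no condition on the date of surgery.
- **Date precision** (Statistical analysis): diagnosis and surgery dates are extracted to the month.

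**The concern.** There are two inconsistencies with one cause: the date of surgery is used where the design needs the date of diagnosis.

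**Entry window.** The setting section and Table 1 cannot both hold for late-2018 diagnoses. If surgery must also fall by 31 December 2018, these patients get less than the full grace period, and their entry depends on how quickly they were operated on. That is information from after time-zero. The Introduction names the alignment of eligibility, treatment allocation and start of follow-up as the reason for emulating a trial.

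**Period covariate.** Year of surgery is not known at diagnosis. The article itself says that surgery on the day of diagnosis is unlikely. A patient diagnosed shortly before the 2009/2010 or 2014/2015 boundary is therefore placed in one guideline period or the next by waiting time. The variable is an adjustment covariate and also defines the period-specific groups, so both uses are affected.

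What is at stake is a consistent eligibility rule, a small selection concentrated in the 2015–2018 group, and a small misplacement at the two inner boundaries.

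**Working it through.** **The plan's own figure.** The article chooses 31 December 2023 as the administrative censor date to secure at least five years of observation. From the last possible diagnosis, 31 December 2018, to that date is 60 calendar months. The figure is reproduced. It depends on the date of diagnosis only, so it gives no reason to cap surgery at 2018.

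**Length of the windows.** 1 January 2008 to 31 December 2018 is 11 × 365 + 3 leap days = 4018 days. 2015–2018 is 4 × 365 + 1 = 1461 days.

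**Grace period left under the literal reading.** Days available = min(90, 31 December 2018 − diagnosis date).

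| Diagnosis date | Days available |
|---|---|
| 2 October 2018 | 90 |
| 3 October 2018 | 89 |
| 1 November 2018 | 60 |
| 1 December 2018 | 30 |
| 31 December 2018 | 0 |

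Diagnoses on 90 calendar days are affected: 90/4018 = 2.2% of all diagnosis days and 90/1461 = 6.2% of those in 2015–2018.

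**An illustration.** Two patients are diagnosed on 1 December 2018. One is operated on 20 December (day 19), the other on 10 January 2019 (day 40). Both meet Table 1. Only the first meets the setting section read literally.

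**Size, under assumptions.** The article gives no waiting times. Assume diagnoses spread evenly over the window and a lognormal wait with median 14, 21, 30 or 45 days and log-SD 0.6, cut off at 90 days. The share dropped at the end of 2018 is then close to mean wait / 4018. The share crossing one of the two inner boundaries is close to 2 × mean wait / 4018. Simulated results:

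| Median wait (assumed) | Mean wait | Dropped, whole cohort | Dropped, of last 90 days' diagnoses | Period differs from diagnosis period |
|---|---|---|---|---|
| 14 d | 16.7 d | 0.43% | 19% | 0.81% |
| 21 d | 24.5 d | 0.62% | 28% | 1.19% |
| 30 d | 33.1 d | 0.83% | 37% | 1.63% |
| 45 d | 43.7 d | 1.09% | 49% | 2.16% |

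Check by formula: 16.7/4018 = 0.42% and 43.7/4018 = 1.09%; doubled, 0.83% and 2.18%. All the dropped patients were diagnosed in the 2015–2018 period, where the same formula gives 16.7/1461 = 1.1% to 43.7/1461 = 3.0%.

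**With entry by diagnosis date only.** The latest admissible operation is 31 December 2018 + 90 days = 31 March 2019. Every patient has the full grace period, follow-up is unchanged, and year of diagnosis always falls in one of the three existing categories.

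**The case against.** **The cap may be loose wording.** It rests on a short phrase in a setting paragraph. Table 1, the fuller specification, puts no calendar limit on surgery, and the Discussion defines the cohort by diagnosis alone. This stands: one cannot say that the plan definitely excludes 2019 operations. But the loose reading does not remove the problem. A patient diagnosed in December 2018 and operated on in January 2019 would be included and have no category, because the surgery-year categories stop at 2018. Either reading needs a correction.

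**Time-zero has a second wording**, the moment at which eligibility is met, which might seem to allow year of surgery as a baseline variable. It does not: Table 1 names the date of diagnosis, and a grace period that runs from diagnosis needs that.

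**Year of surgery may be deliberate.** Practice at the time of operation may drive the choice of modality, and Table 1 speaks of treatment period. This stands in part: changing to year of diagnosis is a trade-off for boundary patients. It does not reconcile the variable with its stated timing.

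**Dates are held to the month.** This stands. The cut-off of 2 October and the day-level example show the logic of the rule; the extracted data cannot resolve them.

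**A reader might infer a material bias in the hazard ratio.** The document does not support that. The date rule is the same for both modalities, so it distorts the contrast only if waiting time differs by modality and is related to survival, and nothing in the article shows either. Urgency is a weak route to such a difference, because the cohort is elective and emergency colectomy is excluded.

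**Conclusion.** Both inconsistencies stand on the text: the surgery window against the 90-day grace period, and year of surgery against the statement that covariates are measured by time-zero. The truncation covers 2.2% of diagnosis days overall and 6.2% of those in 2015–2018. The shares of patients affected, about 0.4–1.1% dropped and 0.8–2.2% changing period, rest on assumed waiting times and evenly spread diagnoses. No shift in the hazard ratio, risk difference or restricted mean survival time has been shown, and no direction of bias.

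The point deserves correction because the rules conflict and the change is cheap, not because the main result is in danger. It is also narrower than it may look. Table 1 already requires surgery within 90 days for the whole cohort, which is itself a selection on what happens after diagnosis. The calendar edge adds a small increment, and moving it leaves that larger question untouched.

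**What to change.** 1. In the study population paragraph, define entry by diagnosis date only (1 January 2008 to 31 December 2018), and state that surgery counts if it falls within the grace period of Table 1.
2. Extract surgery records through March 2019, stated by month because dates are held to the month.
3. Replace year of surgical treatment with year of diagnosis, in the same three categories, for the weights and the period-specific analyses.
4. Use one wording of time-zero throughout: the date of diagnosis, as in Table 1.

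The cost is a few wording changes and three more months of surgery records from the same registry. There is one small analytical price: a few patients near the 2009/2010 and 2014/2015 boundaries are classed by the guideline period at diagnosis, not the one at operation. The censor date and five-year follow-up stay as they are.
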